#### Temperature and acidosis

The patient’s body temperature and blood samples will be collected for blood gas before resuscitation (0 h) and after resuscitation (0.5 h, 1 h, 1.5 h, 3 h, 6 h, 12 h, 24 h, 3 days, 5 days, and 7 days). The acidosis at the above time point in the blood gas results is recorded.

#### Coagulation function, platelet function, and inflammatory mediator level

Blood samples will be collected before resuscitation (0 h) and after resuscitation (1 h, 3 h, 6 h, 12 h, 24 h, 3 days, 5 days, and 7 days) for analysis and recording of coagulation function, viscoelastic method (VEM), and inflammatory mediator level.

#### Shock recurrence rate

The time point of shock recurrence and the cause of shock recurrence will be recorded throughout the study process, and the shock recurrence rate will be calculated.

#### Complications

Complications (ARDS, AKI, TIC, MODS, etc.) that occurred during the entire study process will be recorded and confirmed through corresponding diagnostic methods.

#### Duration of mechanical ventilation, renal replacement therapy

The days of mechanical ventilation, hemodialysis, or hemofiltration are calculated and recorded.

#### Resuscitation fluid and drug usage

The total volume of different fluids used before admission and after entering the study until the 7th day is recorded, including crystals, colloids, blood products, hemostatic drugs, and vasoactive drugs.

#### EICU days and length of stay

Hospital stays and length of EICU days will be recorded. If the patient is hospitalized at any time of the day, that day will be regarded as the hospitalization day. If the patient is in the EICU at any point on the calendar day, that day will be considered EICU day.

#### Surgical episodes

The name, start time, duration, and cause of all surgical episodes will be recorded. In addition to major surgical procedures, this also includes interventional radiology and bedside surgery and operations.

#### Data and safety monitoring

Investigators need to fill in the data collected in the case report form (CRF) according to the requirements of the research program. At the end of the study, the investigator will submit the case reports of all patients selected for this study to the data management center, which should be complete and signed. The consistency of the collected case reports table data will be checked. The inconsistent data will be questioned, and the responsible doctor will be required to clarify. Before starting the trial, unified training will be given to the investigator to clarify the purpose of the study and ensure that the same test methods are used in the trial. The investigator must research in strict accordance with the requirements of the research program. Patients are randomly and distributed by statisticians and data management centers, and the doctor is responsible for in putting information into the case report form. The CRF supervisor will check the completeness and accuracy of the CRF and guide the research center staff to make necessary modifications or supplements. The CRF is sent to the data processing by the regional supervisor, one copy is retained in the research center, and the other one is used as an attachment to the supervisor’s work. CRF will hand it over to a reliable medical data processor for data entry. Data items in CRF will be entered into the research database using a multiple-input method with secondary input audits. Text items (such as comments) can only be checked manually after entering once from CRF. The data manager then systematically checks the information entered into the database using error messages printed from the confirmer program and the database list. The database will be locked after it is declared complete and correct. After that, any changes to the database can only be achieved with the written consent of clinical research leaders, research statisticians, and data managers.

#### Plans to give access to the full protocol, participant-level data, and statistical code

Full protocol, anonymous participant-level data, and statistical code will be shared on reasonable request by scientists.

#### Sample size

The trial design of this study was a positive drug, parallel-group, and superiority verification. The primary endpoint is the duration of shock and lactic acid clearance rate during the early fluid resuscitation period (6 h). Both primary endpoints were required to be met simultaneously, and Bonferroni correction was used as appropriate. The alpha value = 0.025 (one-sided), power = 0.80 were set. The total sample size was finally determined to be 400 cases with 200 cases in each study arm.

The calculations were as follows:Lactic acid clearance rate: According to a study by Wang et al., the mean value of lactic acid clearance rate after 6 h of fluid resuscitation in the control group was 32% with a standard deviation of 10%, and the expected lactic acid clearance rate after 6 h of fluid resuscitation in the test group was 35% with an equal standard deviation for both study arms [42]. The calculated sample size was 176 cases for each study arm, and a total of 392 cases were required based on 10% of the loss to follow-up.Duration of shock: According to the pre-experimental study, the duration of shock in the control group was 3 h, and in the test group the duration of shock was 1.5 h, with a standard deviation of 4 h. Assuming equal standard deviation for both study arms, the sample size calculated for both study arms was 113 cases, and a total of 252 cases were required based on 10% of the loss to follow-up.

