**Methods:**

/design.

This single-center, prospective, randomized controlled trial will focus on the efficacy and safety of BRS in early THS resuscitation. A total of 400 adults THS patients will be enrolled in this study. In addition to providing standard care, enrolled patients will be randomized in a 1:1 ratio to receive resuscitation with BRS (test group) or sodium lactate Ringer’s solution (control group) until successful resuscitation from THS. Lactate clearance at different time points (0.5, 1, 1.5, 3, and 6 h) and shock duration after drug administration will be compared between the two groups as primary end points. Secondary end points will compare coagulation function, temperature, acidosis, inflammatory mediator levels, recurrence of shock, complications, medication use, and 7-day mortality between the two groups. Patients will be followed up until discharge or 7 days after discharge.

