### Outcomes

#### Primary endpoint

(A)Duration of shock(B)Lactic acid clearance rate of 6 h

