#### Statistical analysis

This trial was performed using SPSS 26.0 for data analysis. A general linear model was used to correct for selection bias between the two study arms. Categorical data were described as percentages. The measurement data were tested for normality, approximately normal or normally distributed measures were expressed as mean ± standard deviation (x ® ± s), and non-normally distributed measures were expressed as median (quartiles). The chi-square test/ Fisher’s precision probability test was used for categorical data. Paired *t*-test/rank sum test/one-way repeated measures ANOVA/two-way repeated measures ANOVA was used for the measurement data. Kaplan–Meier survival curves were plotted for survival analysis of patients, and differences between the two study arms were compared using the log rank test. Multiple regression analyses were selected to analyze the interrelationships between the factors. The missing data were handled using the last observation carry forward (LOCF) method, and sensitivity analysis was performed using the multiple imputation method. *P* < 0.05 was statistically significant.

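### The primary success rule is not uniquely fixed: both endpoints are required yet Bonferroni is invoked, the primary lactate time point differs between sections, and the 0.80 power is per endpoint rather than for meeting both

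*Protocol article*

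**What the plan says.** **Success rule and alpha.** The Sample size section states: "Both primary endpoints were required to be met simultaneously, and Bonferroni correction was used as appropriate". The next sentence reads: "The alpha value = 0.025 (one-sided), power = 0.80 were set". The Statistical analysis section closes with P "< 0.05 was statistically significant". It gives no sidedness and does not tie that level to the primary endpoints.

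**Sizing.** Each endpoint is sized on its own.
- Lactate clearance at 6 h: the mean "in the control group was 32% with a standard deviation of 10"%, and the expected mean "in the test group was 35% with an equal standard deviation for both study arms". This gives 176 per arm, or 392 in total after 10% loss.
- Shock duration: 3 h against 1.5 h with an SD of 4 h. This gives 113 per arm, or 252 in total after 10% loss.
- The trial total is set at 400, 200 per arm.

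**Which lactate measure is primary.** The Abstract (Methods) lists "Lactate clearance at different time points (0.5, 1, 1.5, 3, and 6 h) and shock duration after drug administration" as the primary end points. The Objectives also refer to lactate clearance at every time point. The Primary endpoint list has only "Lactic acid clearance rate of 6 h" beside shock duration, and the Sample size section uses the 6 h value alone. Under Detailed outcome measures, the paragraph headed with the 6 h endpoint gives all five times as the measurement schedule.

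**The concern.** Three things that together define a positive trial do not fit one another.

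1. **Threshold.** Bonferroni protects a claim made when either endpoint succeeds. When both must succeed, testing each at full alpha already controls the error, and the price is paid in power. Naming both devices in one sentence, with the qualifier that Bonferroni is used as appropriate, does not tell the analyst which threshold applies. An endpoint with a one-sided p of 0.02 passes at 0.025 and fails at 0.0125.

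2. **Endpoint.** The Abstract and Objectives make a series of five lactate measurements primary; the Outcomes and Sample size sections make one measurement primary. The article gives no rule for combining five times into one decision.

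3. **Power.** The win that the protocol requires is on both endpoints. The stated 0.80 was set for each separately, and the chance of the joint win is not given.

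The trial is open-label (Blinding section), so a success rule that can be settled after the data are seen is a weakness in the primary conclusion. Applying a Bonferroni split to a both-required rule would also give up power for no gain in error control.

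**Working it through.** **Inputs (Sample size section).** Lactate: difference 35 − 32 = 3 points, SD 10. Duration: difference 3 − 1.5 = 1.5 h, SD 4. One-sided alpha 0.025, power 0.80, loss 10%, 200 per arm. No correlation between the endpoints is given, so it is treated as an assumption and varied.

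**Step 1: reproduce the stated sizes.** Normal approximation: n per arm = 2 (z₁₋α + z₀.₈₀)² (SD/difference)².

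- Lactate: 2 × (1.960 + 0.842)² × (10/3)² = 174.4. The noncentral t calculation gives 176 (power 0.801), as stated.
- Duration: 2 × (1.960 + 0.842)² × (4/1.5)² = 111.6. The noncentral t calculation gives 113 (power 0.801), as stated.
- Loss: 176/0.9 = 195.6, so 196 × 2 = 392; 113/0.9 = 125.6, so 126 × 2 = 252. Both match.

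The threshold in the calculation is therefore one-sided 0.025 per endpoint. That fits an unsplit 0.025. It fits equally well a one-sided 0.05 already halved over two endpoints, although the article does not state a 0.05 starting level.

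**Step 2: sizes if 0.025 itself were split.** At one-sided 0.0125, z₁₋α = 2.241. The noncentral t calculation gives 213 per arm for lactate and 137 for duration. Lactate alone would need 213/0.9 = 236.7, so 237 × 2 = 474 patients, more than the planned 400. The stated sizes do not allow for this split.

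**Step 3: power for each endpoint at the planned total.** After 10% loss, 200 × 0.9 = 180 per arm. Noncentrality = difference / (SD × √(2/n)).

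- Lactate: 3 / (10 × √(2/180)) = 2.846; power 0.810.
- Duration: 1.5 / (4 × √(2/180)) = 3.558; power 0.944.

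**Step 4: power to meet both.** Under independence this is the product. Otherwise it comes from a bivariate normal with these marginal powers. It can never exceed the smaller of the two.

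| Evaluable per arm, one-sided alpha each | Lactate | Duration | Both, r = 0 | Both, r = 0.5 | Both, r = 0.8 | Upper limit |
|---|---|---|---|---|---|---|
| 180, 0.025 | 0.810 | 0.944 | 0.765 | 0.785 | 0.803 | 0.81 |
| 200, 0.025 | 0.849 | 0.9625 | 0.817 | 0.831 | 0.844 | 0.849 |
| 180, 0.0125 | 0.724 | 0.904 | 0.654 | 0.688 | 0.713 | 0.724 |

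For example, in the first row 0.810 × 0.944 = 0.765.

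**Step 5: lactate time points.** No arithmetic settles this. Only the 6 h value has a sample size behind it, and only 6 h appears in the formal list of primary endpoints. The Abstract and Objectives state something else.

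**The case against.** The strongest reply has four parts.

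- **The Bonferroni wording is conditional.** Under a both-required rule no correction is appropriate, so the qualifier could be read as meaning none. That is a fair reading, but it is not the only one. The sentence presents the correction as used, and the threshold is never stated per endpoint.

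- **The sizes may already contain a Bonferroni split.** A reader might infer from Step 1 that no correction entered the calculation. The documents do not support that, because a one-sided 0.05 halved over two endpoints gives the same 176 and 113. On that reading the third row of the table does not apply. This part stands, and it limits the conclusion to what the sizes exclude: a split of 0.025.

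- **0.025 against 0.05.** A reader might see a contradiction between the design level and the closing significance statement. There is none as such: one-sided 0.025 and two-sided 0.05 are equivalent. What remains is that the closing statement does not say it is two-sided, a minor clarification that belongs with the main repair.

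- **The power gap is small.** The article does not claim 0.80 as joint power. Positive correlation is plausible because a lactate level of at most 2 mmol/L is among the criteria for successful resuscitation, which ends shock duration. At 180 per arm the shortfall is about 3.5 points at independence and is gone by a correlation of about 0.8; with all 200 per arm evaluable there is none. This stands as a statement of size.

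A reader might also infer that success at any one of the five lactate times counts, with an inflated error rate. No section states such a rule: the Sample size section requires both endpoints and sizes lactate at 6 h. The fault is inconsistent naming of the endpoint, and no error rate can be attached to it from the document.

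**Conclusion.** The concern holds in a limited form. The article requires both primary endpoints while invoking a correction that this rule does not need, so the threshold per endpoint is left open between one-sided 0.025 and 0.0125. It also names two different primary lactate endpoints. These two defects are in the text itself and do not depend on any assumption.

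The power point is real but modest. The 0.80 is per endpoint. Under the protocol's own effect sizes and SDs, with 10% loss and non-negative correlation between the endpoints, the chance of meeting both is 0.765 to 0.81; without loss it is at least 0.817. It becomes material only if 0.025 is actually split, when joint power at 180 per arm would be about 0.65 to 0.72. The correlation values are assumptions, since the article gives none.

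The documents do not establish that Bonferroni is absent from the sample size, that 0.025 and 0.05 conflict, or that the type I error is inflated through the five lactate times.

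**What to change.** State one rule and use it in every section:

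- Lactate clearance at 6 h and shock duration are co-primary. Each is tested at one-sided 0.025, equivalently two-sided 0.05, without Bonferroni. The trial succeeds only if both are met.
- Lactate clearance at 0.5, 1, 1.5 and 3 h is secondary. Align the Abstract and the Objectives with the Primary endpoint list.
- Restate power for 400 patients after 10% loss as about 0.81 for lactate and 0.94 for duration, and about 0.77 to 0.81 for both, with the assumed correlation shown.
- In the Statistical analysis section, say that the P < 0.05 criterion is two-sided.

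The cost is wording and a slightly less favourable stated power. No extra patients or measurements are needed. The change should be made and dated before any comparison of the arms.

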#### Statistical analysis

This trial was performed using SPSS 26.0 for data analysis. A general linear model was used to correct for selection bias between the two study arms. Categorical data were described as percentages. The measurement data were tested for normality, approximately normal or normally distributed measures were expressed as mean ± standard deviation (x ® ± s), and non-normally distributed measures were expressed as median (quartiles). The chi-square test/ Fisher’s precision probability test was used for categorical data. Paired *t*-test/rank sum test/one-way repeated measures ANOVA/two-way repeated measures ANOVA was used for the measurement data. Kaplan–Meier survival curves were plotted for survival analysis of patients, and differences between the two study arms were compared using the log rank test. Multiple regression analyses were selected to analyze the interrelationships between the factors. The missing data were handled using the last observation carry forward (LOCF) method, and sensitivity analysis was performed using the multiple imputation method. *P* < 0.05 was statistically significant.

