**Fig. 2 Fig2:**
[figure not shown]
Schedule of enrolment, interventions, and assessments. ^1^Shock Index, APACHE II, GCS score, ISS score, AIS score, NISS score, SOFA score, CRAMS score. ^2^Sodium bicarbonate Ringer’s solution group. ^3^Sodium lactate Ringer’s solution group

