### Exclusion criteria

Traumatic brain injury (TBI) and brain stem failureSevere cardiopulmonary dysfunctionSevere hepatorenal insufficiencyHypermagnesemiaHypothyroidismUsed acid correction drugsMinorities: pregnant, lactating, and prisonersTreating physician believes the patient is not suitable for the trialInability to obtain consent  Patients automatically gave up treatment or died during the study

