#### Randomization procedure

Enrolled patients will be assigned to the study arm in a 1:1 ratio based on the size of the assigned numbers via a computer-generated random number table within 10 min of admission. Before the study began, a random envelope was prepared for each bed. The envelope contains a card printed with a number (from the random number table). Once the patient is confirmed eligible to participate in the study and informed consent is obtained, the envelope will be opened and unblinding by the investigator immediately after the patient arrives at the bedside. Patient study arm is determined based on the size of the numbers on the card to ensure there is no delay in treating the patient. The investigator will not know the study arm until unblinding takes place and each envelope will be used only once.

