#### Lactic acid clearance rate of 6 h

The lactic acid in the blood gas results is recorded before fluid resuscitation (0 h) and after resuscitation (0.5, 1, 1.5, 3, and 6 h). The lactic acid clearance rate at the above is calculated based on the time point change in the lactic acid.

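### The general linear model is given the task of correcting selection bias, which it cannot be relied on to do in a randomised trial, and the precision available from 0-h lactate is not secured for the primary endpoint

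*Protocol article*

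**What the plan says.** The Statistical analysis section of the protocol article gives the linear model one role: "A general linear model was used to correct for selection bias between the two study arms". For continuous outcomes it then offers a list that starts with the paired t-test and continues "rank sum test/one-way repeated measures ANOVA/two-way repeated measures ANOVA was used for the measurement data". No item on that list is tied to either primary endpoint. A further regression has a different aim: "Multiple regression analyses were selected to analyze the interrelationships between the factors".

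Three other places bear on the point.

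- Randomization procedure: "Enrolled patients will be assigned to the study arm in a 1:1 ratio", using a computer-generated random number table.
- Exclusion criteria, last item: "Patients automatically gave up treatment or died during the study". Neither event can be known at enrolment.
- Lactic acid clearance rate of 6 h: "The lactic acid in the blood gas results is recorded before fluid resuscitation (0 h", so a baseline value of the variable behind the primary endpoint exists. The footnote to Fig. 2 also lists scores collected in the trial: "Shock Index, APACHE II, GCS score, ISS score, AIS score, NISS score, SOFA score, CRAMS score".

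**The concern.** Selection bias means that the groups compared differ systematically because of how patients came to be in them. Sound random allocation removes that at baseline and leaves chance imbalance, which the error rate of the test already allows for. If the bias arises after randomisation, because patients who die or give up treatment are taken out, it runs through prognosis and response to treatment. Baseline covariates capture these only in part. The sentence therefore promises a protection that the model cannot be relied on to give, against a problem that the exclusion list may itself create.

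The sound reason for a linear model here is different: it takes out the part of the outcome variance that the starting value explains. The article does not state that reason and ties no such model to the primary endpoint. The 6-h clearance endpoint is planned at 80% power and both primary endpoints must succeed, so extra precision that costs no patients is worth securing.

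**Working it through.** **1. The plan's own sample sizes (section Sample size).** Inputs are one-sided alpha 0.025 and power 0.80. For lactate clearance the means are 32% and 35% with SD 10%; for shock duration they are 3 h and 1.5 h with SD 4 h.

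n per arm = 2 (1.960 + 0.842)² / (difference/SD)²

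- Clearance: 2 × 7.849 / 0.30² = 174.4, or 175.4 with the t distribution, rounded up to 176. With 10% loss: 176 / 0.9 = 195.6, so 196 per arm and 392 in total.
- Shock duration: 2 × 7.849 / 0.375² = 111.6, or 112.6 with the t distribution, rounded up to 113. With 10% loss: 113 / 0.9 = 125.6, so 126 per arm and 252 in total.

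Both stated figures reproduce. Both are for unadjusted two-group comparisons.

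**2. What adjustment for 0-h lactate could add.** With correlation r between covariate and outcome within arms, the residual SD is SD × √(1 − r²), and the standardised difference becomes 0.30 / √(1 − r²). There are 200 × 0.9 = 180 evaluable patients per arm. Approximate power is Φ(standardised difference × √90 − 1.960). The article gives no r, so the values are assumed.

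| r (assumed) | Variance removed (r²) | Standardised difference | × √90 | Power (t distribution) |
|---|---|---|---|---|
| 0 | 0% | 0.300 | 2.846 | 81% |
| 0.3 | 9% | 0.314 | 2.983 | 85% |
| 0.4 | 16% | 0.327 | 3.105 | 87% |
| 0.5 | 25% | 0.346 | 3.286 | 91% |

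For shock duration, unadjusted power at 180 per arm is already 94%, so there is little to gain there.

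**3. Whether adjustment undoes removal after randomisation.** This is an illustration in which every input is assumed. There is no true effect, with 200 per arm and outcome SD 10. An unmeasured severity has correlation 0.5 in size with the outcome (higher severity, lower clearance). The most severe 20% are removed from the test arm and the most severe 10% from the control arm. A measured baseline covariate has correlation 0.5 with the outcome but is unrelated to the severity that drives removal.

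Among those kept, mean severity is −φ(0.842)/0.8 = −0.350 in the test arm and −φ(1.282)/0.9 = −0.195 in the control arm. The false difference in clearance is 10 × 0.5 × (0.350 − 0.195) = 0.77 points. Simulation with 2,000 runs gave 0.79 unadjusted and 0.81 adjusted; with 20,000 runs it gave 0.77 for both. The adjusted test rejected in 14% to 15% of runs against a nominal 2.5%. Against a planned effect of 3 points, the bias is about a quarter (0.77 / 3 = 26%), and adjustment left it unchanged.

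The setting was chosen to show the limit. If the covariate carried part of the severity that drives removal, adjustment would take out part of the bias. How much is unknown, which is why the model cannot be relied on.

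**4. Whether choosing covariates would inflate the error rate.** This was simulated under no effect with 8 candidate covariates, r = 0.3 each (assumed), 180 per arm, 20,000 runs and nominal 2.5%.

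| Rule | One-sided rejection |
|---|---|
| Unadjusted test | 2.6% |
| Fixed model with all 8 | 2.3% |
| Adjust only for covariates that differ significantly between arms | 1.7% |
| Most favourable of the unadjusted, full and single-covariate models | 7.7% |

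Inflation comes from picking the favourable result. Adjusting for observed imbalance was conservative on its own.

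**The case against.** The strongest reply is that the sentence is poor wording for a sound method. A general linear model with baseline covariates is analysis of covariance, the model asked for here. The covariate list and the choice of primary model commonly sit in a statistical analysis plan or full protocol, and neither is shown. The lactate endpoint reaches its planned 80% power without adjustment. Clearance is already calculated from the change since 0 h, so its remaining correlation with starting lactate could be small.

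Much of this stands. The absence of a covariate list is not a fault of the article. A reader might infer three stronger things, none of which the article supports.

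- **That covariates will be picked after looking at imbalance, inflating the type I error.** The article states a purpose and no selection rule. The 7.7% needs deliberate picking of the best result, which is not planned.
- **That precision is thrown away.** The model may well include 0-h lactate; the article only fails to secure it.
- **That all patients meeting the Stopping criteria leave the analysis.** That section does not say so. Last observation carried forward and multiple imputation are planned, which suggests that some incomplete patients are kept. Only the last exclusion criterion clearly suggests removal.

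What the reply does not meet is the stated aim. No covariate list in another document would make correction of selection bias a valid task for this model in a randomised comparison.

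**Conclusion.** The point holds in a limited form. The stated purpose of the model is wrong, and this rests on the article's own words set beside its randomisation and its last exclusion criterion. It needs no assumed figure. The illustration of removal (about 0.8 points of bias, unchanged by adjustment) shows how the promise can fail under assumed inputs; it does not predict this trial.

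The precision argument is secondary. Power for 6-h clearance would rise from about 81% to between 85% and 91%, conditional on a correlation of 0.3 to 0.5 that the article does not give. With a correlation near zero the gain vanishes. No stated sample size is wrong and the trial is not underpowered on this account. The change is worth making because it removes a false assurance and fixes one primary model at no cost in patients or data.

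**What to change.** In the Statistical analysis section, delete the phrase on selection bias and put in its place wording such as:

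> The primary analysis of 6-h lactate clearance is an analysis of covariance of all randomised patients in the arm to which they were assigned, with arm and 0-h lactate as covariates. Any further baseline covariates for either primary endpoint are fixed before outcome data are seen. Unadjusted tests are supportive.

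Which further covariates to use, if any, is for the trial team. Nothing in the article favours particular ones among the scores listed under Fig. 2, and each should be checked to be a pre-randomisation value. The last exclusion criterion has to be reconciled with analysing all randomised patients, and the plan must say how a patient without a 6-h lactate value enters the model.

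The cost is wording. The 0-h lactate is already collected, and the general linear model is already part of the plan.
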